#### Qualitative data

We will conduct interviews with the counsellors, peer mentors, and participants from all intervention groups to perform a process evaluation. We will focus on barriers and enablers to participation in the study to understand how interventions might effectively translate to a community setting. Questions will be posed regarding feasibility, acceptability, perceived utility, and perception of capabilities, opportunities, and motivations (i.e., components of the COM-B model [24]). Throughout the study, we will also follow up with participants who have missed multiple sessions or have dropped out altogether to record reasons for absence or drop-out. This part of our method will provide a more comprehensive picture of the challenges faced by low SES individuals participating in online smoking interventions. Qualitative analysis will follow a three-phase method: pre-coding; conceptual and thematic categorisation; and theoretical categorisation. [63]

#### Intervention fidelity

We aim to determine intra- and inter-individual variability for intervention session delivery between facilitators. The three facilitators will record sessions of each of the three interventions as they are administered to the first cohort of participants. A member of the research team will review the recordings and apply a bespoke rating system which will assess adherence to the content of the program. Participant engagement and facilitator competence will be gauged during the interview process described above.

### Procedures

Figure 2 provides an outline of the study design and Table 1 summarises the data collection protocol for secondary outcomes.

**Fig. 2 Fig2:**
[figure not shown]
Flow diagram—overview of the procedure

**Table 1 Tab1:**
[figure not shown]
Data collection excluding primary outcome

*Start of qualitative data collection determined by participant drop-out

**Setting realistic goals intervention only; initial assessment occurs in week 5

***Mindfulness-based interventions only; week-based intervals have been approximated into months for clarity

#### Screening and group allocation

Prospective participants will complete an online screening questionnaire that addresses the inclusion criteria through Qualtrics. If eligible, they will be asked to give informed consent. Participants will be randomly allocated to one of the three interventions or a control group using computerised sequence generation within the Qualtrics survey (Mersenne Twister algorithm [64]). All participants will complete a baseline questionnaire (see Table 1). Intervention-group participants will then be divided in groups of between 2 and 7 participants within each of the intervention groups (MiCBT, MT, SRG) based on their availability for session times throughout the week.

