## Methods

The following protocol (version 5, September 9th 2022) follows SPIRIT guidelines for reporting protocols (see Additional file 1). In this four-arm parallel-group RCT of SRG, MT and MiCBT versus an active control (equal allocation ratio), we will deliver the interventions to small groups of smokers to maximise the potential cost-effectiveness. 6-months of these interventions will be followed by 6-months of online peer support and a further 6-month follow-up period. The control group will be directed to optional resources including counselling (Quitline) and information about pharmacological aid. We aim to: (a) test the efficacy of the three interventions (SRG, MT and MiCBT) for smoking cessation and (b) levels of resilience in low SES groups and how this changes during exposure to the interventions, (c) measure the cost-effectiveness and cost-utility of the interventions in low SES groups, and (d) undertake a process evaluation of the different interventions in low SES groups. We hypothesise the following:H1: The proportion of participants who report 14-day period abstinence from smoking at 6 months will be significantly higher for each intervention group compared to the control group.H2: Amongst participants that report 14-day period abstinence at 6 months, the proportion of participants who report 14-day period abstinence at 12 months will be significantly higher for each intervention group compared to the control group.H3: The proportion of participants who report 14-day period prevalence abstinence from smoking at 6 months post-trial (18 months from baseline) will be significantly higher for each intervention group compared to the control group.H4: Levels of resilience measured by the Connor-Davidson CD-25 [43] and ENRICHD Social Support Inventory [44] will be significantly higher for each intervention group compared to the control group at 6, 12 and 18 months post randomisation.H5: The interventions will improve smoking cessation and QALYs at a reasonable and acceptable incremental cost.

In addition, we pose the following research questions for the qualitative component of the study (that pertains to the process evaluation):RQ1: Have the different interventions been implemented and received as intended?RQ2: What are the barriers and facilitators associated with the first research question?RQ3: For whom, and in what circumstance were the interventions effective (and cost-effective) or not, and why?

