### Participants

We aim to recruit 812 low SES smokers Australia-wide using web-based advertisments. Inclusion/exclusion criteria for this study will require that participants will be aged 18 years or older and have smoked regularly for at least the previous two years, as assessed by the question: “are you a regular smoker (i.e., you have usually smoked at least one cigarette per day for at least the last two years)?” We will only include smokers who are planning to quit, i.e., they answer yes to the question, “are you currently planning to quit smoking cigarettes?” This indicates that the participant is in the preparation stage of the Transtheoretical Model and getting ready to progress to action. [45] Participants must also have a smartphone, have regular internet access, and be willing to spend approximately 14–20 h online to complete the study over an 18-month period.

We define low SES using household income and access to Australian welfare benefits. Smokers will be included if either (a) their weekly household income is below $457 per adult before tax (the Australian poverty line; [46]) or (b) they receive social security benefits, e.g., aged or low-income pension, parenting payments, or disability support payments. Participants will be recruited from all Australian states and territories using online advertisements on social media and news stories on local radio and television. Recruitment will also be promoted via the networks of Project Reference Group members and other stakeholders providing services to low SES populations. Recruitment began on the 3rd of May 2021, and we aim to continue recruitment until the target sample size is reached.

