#### Phase 1 (months 0–6): group-based interventions

Participants allocated to interventions will attend eight 1-h group sessions online via Zoom over a 6-month period according to a prescribed ideal delivery schedule. Participants will be asked to provide approval these sessions to be recorded (so that they may provide data for analysis regarding intervention delivery, as described above). The facilitators running the interventions will have formal qualifications in CBT and will receive specialised training from experts in mindfulness training and setting realistic goals.

To ensure that all participants are encouraged to access the current best practice approach to smoking cessation, the Royal Australian College of General Practitioner’s [65] “Ask, Advise, Help'” model for smoking cessation will be offered to all participants from baseline, including active control group participants. This approach involves referral to behavioural counselling and provision of information on accessing Nicotine Replacement Therapy and stop-smoking medications where indicated. The behavioural counselling offered in the current study is via the Quitline service.

##### Arm 1

MiCBT is a four-stage therapeutic approach. [66] Therapy begins at the personal stage, with the internal promotion of experiential awareness and acceptance. The second stage introduces imaginary and in vivo exposure procedures, and the third stage extends mindfulness principles into interpersonal interactions. Stage four, the empathetic stage, involves developing ethical awareness and compassion, which is intended to help prevent relapse through counterconditioning. The approach is based on *Vipassana* (insight training) and the co-emergence model of reinforcement. This model proposes that operant behaviour is reinforced by the interoceptive feedback (i.e., conscious or unconscious bodily sensation) which co-emerges with self-referential cognitions, rather than the environmental consequences posited by Skinner. [67] Participants undergoing MiCBT will also be asked to complete 30—60 min of homework daily, including mindfulness practice twice daily and some readings. Homework will be guided by a smartphone application.

##### Arm 2

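### Session availability is first used after randomisation and only in the three group arms, so participants with no workable slot are identified on the intervention side alone

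*Protocol article*

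**What the plan says.** The Participants section lists the practical entry conditions. "Participants must also have a smartphone, have regular internet access", and they must "be willing to spend approximately 14–20 h online to complete the study over an 18-month period". Being free at an offered session time is not among them.

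Screening and group allocation then gives the order of events. "Prospective participants will complete an online screening questionnaire that addresses the inclusion criteria through Qualtrics". Eligible people consent, and "Participants will be randomly allocated to one of the three interventions or a control group using computerised sequence generation within the Qualtrics survey". A baseline questionnaire follows for everyone. Only then does availability appear: "Intervention-group participants will then be divided in groups of between 2 and 7 participants within each of the intervention groups", "based on their availability for session times throughout the week".

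The arms differ in what they need from a timetable. Under Phase 1, "Participants allocated to interventions will attend eight 1-h group sessions online via Zoom over a 6-month period". For control, the opening of Methods says "The control group will be directed to optional resources including counselling (Quitline) and information about pharmacological aid", which needs no group and no slot.

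The Analyses subsection makes the per-protocol analysis the main one. It defines the intention-to-treat population as everyone randomised who completed the baseline survey, uses a modified intention-to-treat analysis for sensitivity, and counts missing smoking data as continued smoking. The Discussion adds that people who drop out are still followed for data.

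**The concern.** Whether a person can attend a live weekly group is a feasibility condition that applies to every candidate before allocation. The stated order turns it into a step that operates after allocation and in three of the four arms. Someone whose hours match no offered session, or who is the only person in an arm able to make a given slot (the minimum group size is 2), comes to light only if allocated to an intervention. The same person allocated to control is never recognised.

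What is at stake depends on how such people are analysed. Kept in their allocated arm, they are untreated members of it and pull its abstinence rate towards control. Left out of a per-protocol analysis, they are removed from the intervention side while their counterparts stay in control, and the contrast is no longer purely the randomised one. Since the main analysis is per protocol, the second route is the more worrying.

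**Working it through.** **Inputs from the Sample size and power analysis section:** control abstinence p₀ = 13.6%; intervention abstinence p₁ = 25.2%; difference 11.6 points; 182 per group; two-sided alpha 0.05; 80% power; 10% drop-out; 203 per group; N = 812.

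**Inputs that are assumptions:** the share u of an intervention arm that cannot be placed, taken as 1%, 5% and 15%; and the abstinence rate of those people. The documents give neither.

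**Step 1: the plan's own figure.** Two-proportion normal approximation, pooled variance under the null, no continuity correction:

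n = [1.960·√(2·p̄(1−p̄)) + 0.842·√(p₀(1−p₀) + p₁(1−p₁))]² / (p₁−p₀)², with p̄ = (0.136 + 0.252)/2 = 0.194.

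The square roots are 0.5592 and 0.5532, so n = 181.2, rounded up to 182. Power at 182 is 80.2%. Then 182/0.90 = 202.2, rounded up to 203, and 4 × 203 = 812. The stated numbers reproduce.

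**Step 2: unplaced people are kept and quit at the control rate.** The intervention rate becomes p₁(1−u) + p₀u, so the difference is 11.6 × (1−u) points.

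| u | Intervention rate | Difference (points) | Power, 182 per group |
|---|---|---|---|
| 0 | 25.2% | 11.6 | 80.2% |
| 1% | 25.1% | 11.5 | 79.5% |
| 5% | 24.6% | 11.0 | 76.5% |
| 15% | 23.5% | 9.9 | 67.9% |

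Across the three intervention arms (3 × 203 = 609 people) these shares correspond to about 6, 30 and 91 participants. This is dilution: the arms are still the randomised ones.

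**Step 3: unplaced people are dropped from the intervention side, with no true effect.** Let them have abstinence q, assumed to be half the control rate (6.8%). The placed remainder then quits at (p₀ − u·q)/(1−u), while control still shows p₀.

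- u = 1%: (0.136 − 0.01 × 0.068)/0.99 = 0.1367, a gain of 0.07 points (about 0.1).
- u = 5%: (0.136 − 0.05 × 0.068)/0.95 = 0.1396, a gain of 0.36 points (about 0.4).
- u = 15%: (0.136 − 0.15 × 0.068)/0.85 = 0.1480, a gain of 1.2 points.

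The sign depends on q. If unplaced people would quit more often than average, the bias runs against the intervention.

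**Step 4: unplaced people are kept but give no smoking data.** They are then counted as smokers. With no true effect, the intervention arm loses u × 13.6%: 0.1, 0.7 and 2.0 points at 1%, 5% and 15%. Follow-up of people who leave the intervention is meant to limit this.

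**The case against.** The article does not say that anyone will be unplaceable. Groups are built around stated availability, the demand is eight one-hour online sessions, a group may be as small as two, and recruitment continues, so a lone participant may be joined later. The willingness criterion of 14–20 hours also screens out some people short of time. All this stands, and the share may be small: at 1–2% unplaced, power is 79.5–78.7%, a trivial loss. The criterion does not remove the problem, because total hours differ from being free at a particular slot.

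The power figures can also be read as pessimistic. The 182 is the number left after 10% drop-out, and unplaced people may be part of that drop-out. With all 203 per group retained, power is 80.9% at 5% unplaced. That is fair, although the allowance is the same in every arm and does not address a mechanism that works in three of the four.

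Three stronger readings are tempting and are not supported:

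- A reader might infer that unplaced participants are lost. The intention-to-treat definition does not require placement in a group, and drop-outs continue to be followed.
- A reader might infer that the arms stop being comparable whatever is done. If everyone is kept, randomisation still protects the comparison and only the effect is diluted.
- A reader might infer that every comparison is affected in this one-sided way. Between two intervention arms the step applies on both sides, so the point concerns each intervention against control.

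Finally, a condensed article may leave out the rule for a person without a slot, and it does not say exactly when availability is asked. The point does not rest on that silence. It rests on the stated entry criteria, the stated order, and the choice of a per-protocol main analysis.

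**Conclusion.** The point holds in a limited form. Availability is not an entry criterion, is first used after allocation, and is used in three of the four arms. For each intervention against control, this dilutes the effect if unplaced people are kept. It can bias the contrast if they fall outside the per-protocol main analysis, which is the plausible outcome for someone who never had a group to attend.

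The size is unknown, because it rests on an assumed unplaced share with no anchor in the documents and, for the bias, on an assumed abstinence rate among those people. Over 1% to 15%, the results run from negligible to moderate: power between 79.5% and 67.9%, or a spurious gain of about 0.1 to 1.2 points. The planned sample size is correct as calculated. This is a cheap improvement to the design, not a flaw that invalidates it.

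**What to change.** For remaining recruits, put the question on availability for the offered session times in the screening form before randomisation. Require at least one workable slot of every candidate, whichever arm follows, and use the recorded answers to form the groups. With no unplaced participants, the stated 182, 203 and 812 are unchanged.

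This cannot prevent someone being the only person in an arm for a slot, since that depends on who else is allocated there. So also keep every randomised participant with a completed baseline survey in the primary comparison, in the allocated arm, placed or not. Report the number unplaced by arm, including for those already randomised.

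The cost is modest but real. The team already needs the availability answers to form groups. A few smokers with no workable slot are excluded, so the target population must be stated as those able to attend. Recruitment began in May 2021, so eligibility would change part-way through, and the date of the change should be recorded.

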### Sample size and power analysis

For the primary outcome of smoking cessation, 182 participants per group is powered to detect an 11.6% difference [47] in the smoking abstinence rates between groups (with 80% power, alpha = 0.05 (two-tailed test) We will account for a 10% drop-out rate, and thus aim to recruit 203 per group (N = 812). Contextually, the smoking cessation rates we used for the sample size calculation (MT = 25.2%, usual care = 13.6%) represent a meaningful population health treatment effect doubling of the rate of successful quit attempts for the lowest SES group (11.4%; [9]).

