#### Analyses

All analyses will use Stata (version 17.0 [69]). This will be undertaken blinded to the participants’ group allocation. Mixed-effects modelling will be used to assess the effect of the interventions on primary and secondary outcomes. This approach accounts for the correlation of the data from repeat measures over time and reduces bias caused by missing data at one or more time points for each participant. In addition, we will develop prediction models to determine whether levels of internal and external resilience measured at baseline predict smoking cessation. As an exploratory analysis, we will also perform mediation analyses to determine the direct and indirect effects of the separate components of each intervention on the primary and secondary outcomes.

For outcomes assessed at a single time-point, we will assess the difference between the four groups at that time. For outcomes assessed at repeat time points, we will assess differences between the four groups at each time point, with adjustment for multiple comparisons. We will assess binary outcomes using mixed-effects logistic regression and continuous outcomes using linear mixed-effects regression. In repeated measures, we will treat time as a categorical variable, and the model will include fixed-effects for time and group. Subgroup analysis will be undertaken to test whether people with a critical level of resilience are more likely to stay quit than those that do not meet this level. The main analyses will be performed on a per-protocol basis. Our intention-to-treat population will be defined as all participants that were randomised and also completed the baseline survey. We will perform a sensitivity analysis on a modified intention-to-treat basis and impute missing data where possible. Where more than 10% of data are missing, we will also perform multiple imputation as a sensitivity analysis to account for possible bias in estimates caused by missing data. Missing smoking data will be presumed MNAR and analysed as continued smoking. Hypothesis testing will be performed using 2-tailed tests with a Type 1 error rate of alpha = 0.05, and 0.05/3 = 0.0167 when assessing each outcome across time to account for the repeated testing at 6, 12, and 18 months. We will make further adjustments for multiple comparisons (e.g., 3 comparisons with control) depending on each outcome.

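### Session-group clustering in the three intervention arms is allowed for neither in the sample size nor in the model described; if outcomes correlate within groups, comparisons with control are anti-conservative and power falls below 80%

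*Protocol article*

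**What the plan says.** All of the following is in the protocol article.

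- **Design (Methods).** Four parallel arms are individually randomised, three interventions "versus an active control (equal allocation ratio").
- **Grouping (Screening and group allocation).** After randomisation and the baseline questionnaire, "Intervention-group participants will then be divided in groups of between 2 and 7 participants within each of the intervention groups", according to when people are available.
- **Exposure (Phase 1).** "Participants allocated to interventions will attend eight 1-h group sessions online via Zoom over a 6-month period". The primary outcome is abstinence at 6 months, so the group course falls entirely before it. The control arm is pointed to optional resources such as Quitline and is not formed into groups.
- **Sample size (Sample size and power analysis).** "182 participants per group is powered to detect an 11.6% difference" in abstinence, "with 80% power, alpha = 0.05 (two-tailed test"), from rates of "MT = 25.2%, usual care = 13.6%". Then: "We will account for a 10% drop-out rate, and thus aim to recruit 203 per group (N = 812"). No ICC or design effect is given.
- **Model (Analyses).** Mixed-effects logistic or linear regression is planned. The correlation it is said to handle is within-person: "This approach accounts for the correlation of the data from repeat measures over time". The fixed effects are time and group, where group means the four trial arms.

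No effect of session group or facilitator on the outcomes is mentioned in the analysis or sample-size text.

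**The concern.** This is a partially nested design: clustering arises after randomisation and in the intervention arms only. People who go through a six-month course together may end up with more similar outcomes than people who do not. The article itself describes mechanisms. Participants in the goal-setting arm work together on their goals (Phase 1, Arm 3), and the fidelity section expects delivery to vary between facilitators.

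With a positive ICC, the variance of an intervention-arm estimate exceeds the independent-data variance. A model that ignores this gives standard errors that are too small for comparisons with control. A model that respects it has less power than stated. At stake are the abstinence comparisons (H1 to H3) and the resilience comparisons (H4), each of which sets a grouped arm against an ungrouped one. The sample size has no slack to absorb the loss: its power is 80.2% before the multiplicity adjustments that the article also promises.

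**Working it through.** **Inputs from the article.** p1 = 0.252, p2 = 0.136, two-sided alpha 0.05, power 80%, 182 per arm, 10% drop-out, session groups of 2 to 7.

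**Assumptions, because the article gives no figure.** ICC 0.01 to 0.10; mean group size m = 4.5 (midpoint of 2 and 7).

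**Step 1: reproduce the plan's sample size, treating participants as independent.** With p̄ = (0.252 + 0.136)/2 = 0.194:

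n = [1.960 × √(2 × 0.194 × 0.806) + 0.842 × √(0.252 × 0.748 + 0.136 × 0.864)]² / 0.116²
= [1.960 × 0.5592 + 0.842 × 0.5532]² / 0.013456 ≈ 181.2, which rounds up to 182.

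182/0.9 = 202.2, which rounds up to 203, and 4 × 203 = 812. All three stated figures are recovered, so they contain no allowance for clustering. Power at 182 per arm is 80.2%.

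**Step 2: inflate the intervention-arm variance only.** DE = 1 + (m − 1) × ICC.

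- Standard error under the null: SE0 = √[p̄(1 − p̄)(DE + 1)/n]
- Standard error under the alternative: SE1 = √{[p1(1 − p1) × DE + p2(1 − p2)]/n}
- Power = Φ[(0.116 − 1.960 × SE0)/SE1]

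Example with m = 4.5 and ICC 0.05: DE = 1 + 3.5 × 0.05 = 1.175. SE0 = √(0.156364 × 2.175/182) = 0.04323. SE1 = √[(0.188496 × 1.175 + 0.117504)/182] = 0.04316. Power = Φ[(0.116 − 0.08473)/0.04316] = Φ(0.725) = 76.6%.

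**Step 3: type I error if clustering is ignored.** Under the null the true standard error exceeds the naive one by the factor r = √[(DE + 1)/2], so the actual two-sided error is 2 × [1 − Φ(1.960/r)]. In the example, r = √1.0875 = 1.043 and the error is 6.0%.

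| m | ICC | DE | Power at 182 per arm | Type I error if ignored |
|---|---|---|---|---|
| 2 | 0.01 | 1.010 | 80.0% | 5.1% |
| 2 | 0.05 | 1.050 | 79.1% | 5.3% |
| 2 | 0.10 | 1.100 | 78.1% | 5.6% |
| 4.5 | 0.01 | 1.035 | 79.4% | 5.2% |
| 4.5 | 0.05 | 1.175 | 76.6% | 6.0% |
| 4.5 | 0.10 | 1.350 | 73.2% | 7.1% |
| 7 | 0.01 | 1.060 | 78.9% | 5.3% |
| 7 | 0.05 | 1.300 | 74.1% | 6.8% |
| 7 | 0.10 | 1.600 | 68.7% | 8.6% |

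**Step 4: what would restore 80% power at ICC 0.05, with equal allocation.** At m = 4.5, 199 per arm, or 222 after drop-out, N = 888. At m = 7, 211 per arm, or 235 after drop-out, N = 940.

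**Step 5: sensitivity to the group-size assumption.** Two refinements pull in opposite directions.

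- Applying the planned 10% drop-out to group size gives m = 4.5 × 0.9 = 4.05. Power is then 77.0% at ICC 0.05 and 74.0% at ICC 0.10, with type I errors of 5.9% and 6.8%.
- If sizes 2 to 7 are equally likely, their coefficient of variation is √(35/12)/4.5 = 0.38. Using DE = 1 + [(1 + 0.38²) × 4.5 − 1] × ICC, power is 75.9% at ICC 0.05 and 72.0% at ICC 0.10, with type I errors of 6.2% and 7.4%.

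Neither changes the picture.

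**The case against.** The best defence has four parts.

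1. **The model text is not exhaustive.** The article gives correlation over time as a reason for mixed models but does not say it is the only correlation modelled. It leaves the random-effects structure unspecified, and a statistical analysis plan that is not shown could add a session-group term. This stands as a limit on how firmly the model can be faulted. It does not remove the point: the article goes far enough to name the correlation handled and the fixed effects, and that description does not fit the delivery it sets out elsewhere. Nor can a later analysis plan put an allowance into a sample size already set.

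2. **Some tempting facts are not in the text.** A reader might infer that groups are fixed, that each keeps one facilitator, and that membership is already on file. The article says only that participants are divided by availability and attend eight sessions. Stable membership is a fair inference; a constant facilitator and an existing membership record have no textual support. None of the figures needs a constant facilitator.

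3. **The harm is conditional and may be small.** It needs a positive ICC, for which the article gives no value. At ICC 0.01, or with groups of two, it is negligible. The largest figures need the top of the assumed ICC range and every group at the maximum size. This stands in full.

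4. **Not every outcome is affected in this way.** Equanimity is measured only in the two mindfulness arms and goal attainment only in the goal-setting arm, so the control-comparison figures do not apply to them. This also stands.

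On the other side, shared facilitators and the intervention-specific peer forums of months 6 to 12 could add correlation that these figures leave out.

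**Conclusion.** The point holds in conditional form. It is established that the sample size assumes independent participants, because 182, 203 and 812 follow exactly from that formula. It is also established that the described model names only repeat-measures correlation. It follows that, for any positive within-group ICC, tests of intervention against control run as described are anti-conservative and 182 per arm gives less than the calculated 80.2% power.

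The size rests on assumptions. At a mean group size of 4.5 and ICC 0.01 to 0.10, power is 79.4% to 73.2% and type I error 5.2% to 7.1%. The far end of the range examined (size 7, ICC 0.10) gives 68.7% and 8.6%.

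A reader might go further and conclude that the trial's standard errors are certainly too small, or that all its secondary tests are inflated. The article does not support either: it reports no ICC, does not rule out a session-group term, and does not measure every outcome in controls. The plan should be changed, but the defect is moderate and does not by itself undermine the trial.

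**What to change.** 1. **Record session-group membership** for every intervention participant, including any change of group during the course.
2. **For outcomes compared with control, fit a partially nested mixed model.** Use a session-group random effect in the three intervention arms only, treat each control as a group of one, and nest the participant effect within it for repeated measures. For abstinence this is a three-level logistic model with some very small groups and may not converge. Name the fallback in advance: cluster-robust standard errors by session group, with controls as singletons.
3. **Restate power at 182 per arm over a range of assumed ICCs**, for example about 77% at ICC 0.05 and mean size 4.5, before multiplicity adjustment.

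The cost is keeping a record of group membership, a somewhat more complex model, slightly wider intervals and a slightly lower stated power. No extra data are needed from participants. If the ICC proves close to zero, little is lost.
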